### Electroencephalography (EEG) recording

The EEG recording procedure will include rest, listening to the TIMP music patterns (that will be learned in the sessions) a Go/No go task, after which another resting state EEG will be recorded. This study will utilize a BrainAmp DC (Brainproducts) EEG utilizing 64 active electrodes and artifact channels (EOG, EMG). Artifact control will be guided by video recording of the participant whilst undergoing EEG. The video footage will inform about body movement and eye-blinks. After visual inspection and indexing of the continuous EEG traces, data pre-processing will utilize the Neuroguide Artifact toolbox (Thatcher et al., 2009) for the resting EEG and the music listening task. EEGLAB and ePrime will be used for the analysis of the Go/No Go task and will focus on the short episodes around the clicks. After visual inspection ICA will be applied to pre-process data and determined artifacts will be excluded.

### Semi-structured interviews

Using the principles and processes described in Interpretative Phenomenological Analysis (IPA) (Smith and Osborn, 2008) material from the semi-structured interviews will be analyzed into themes. The questions have been designed as open questions to encourage participants to offer descriptions of their experience of playing the instruments and playing to the supporting music. In keeping with IPA principles, the underlying aim of the questions is to offer participants a chance to explain how they feel the treatment will affect them and describe how they are experiencing, feeling and thinking about the processes involved, as such this will provide data regarding motivation and emotional response. Patient feedback in these areas will also feed into questions around feasibility of delivery for this treatment protocol.

### Statistical analysis

For the primary outcome measures, for the appropriate analysis of the crossover design with repeated measures, a linear mixed model approach will be used. This will be undertaken using the computer program R and will employ the R package lme4, which is sufficiently flexible to provide detailed analysis for this type of design, including the accommodation of missing values. The main result of this analysis will be the assessment of whether the music therapy has had an effect. To avoid the need to make strong assumptions about the distribution of the data, namely, that fitted model residuals are Normally distributed, computer-intensive methods will be employed for the statistical inferences. This will include bootstrap approaches to calculating 95% confidence limits, and permutation tests to obtain statistical significance test *P*-values.

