## Abstract

**Background:** Impairment of upper limb function following stroke is more common than lower limb impairment and is also more resistant to treatment. Several lab-based studies with stroke patients have produced statistically significant gains in upper limb function when using musical instrument playing and techniques where rhythm acts as an external time-keeper for the priming and timing of upper limb movements.

**Methods:** For this feasibility study a small sample size of 14 participants (3–60 months post stroke) has been determined through clinical discussion between the researcher and study host in order to test for management, feasibility and effects, before planning a larger trial determined through power analysis. A cross-over design with five repeated measures will be used, whereby participants will be randomized into either a treatment (*n* = 7) or wait list control (*n* = 7) group. Intervention will take place twice weekly over 6 weeks. The ARAT and 9HPT will be used to measure for quantitative gains in arm function and finger dexterity, pre/post treatment interviews will serve to investigate treatment compliance and tolerance. A lab based EEG case comparison study will be undertaken to explore audio-motor coupling, brain connectivity and neural reorganization with this intervention, as evidenced in similar studies.

**Discussion:** Before evaluating the effectiveness of a home-based intervention in a larger scale study, it is important to assess whether implementation of the trial methodology is feasible. This study investigates the feasibility, efficacy and patient experience of a music therapy treatment protocol comprising a chart of 12 different instrumental exercises and variations, which aims at promoting measurable changes in upper limb function in hemiparetic stroke patients. The study proposes to examine several new aspects including home-based treatment and dosage, and will provide data on recruitment, adherence and variability of outcomes.

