## Methods

### Study design

A cross-over design with repeated measures will be used, with participants being randomized into either a wait list or treatment group (see Figure 1). Assessments for each participant will take place at the same time points after baseline measure, as illustrated in Figure 1, with the baseline and end assessments immediately before and after the 6 weeks of TIMP being conducted by a therapist who is blind to participant allocation.

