### Procedure

Each participant will have a total of 12 individual music therapy sessions in their home, delivered twice weekly over the course of 6 weeks. They will not be required to perform any practice or exercises set by the researcher between sessions. Whilst in wait list, before the intervention begins, participants will not receive any community nor privately employed rehabilitation interventions for upper limb hemiparesis. Each participant will also receive the Action Research Arm Test (ARAT) (Lyle, 1981) and Nine Hole Peg Test (9HPT) (Kellor et al., 1971) assessments at the same five time points after baseline measure, over an 18 week period as follows: Timepoint 1 at Week 1 after randomization; timepoint 2 at week 6; timepoint 3 at week 9; timepoint 4 at week 15; and timepoint 5 at week 18. The design will allow analysis of treatment and no treatment by comparing treatment group with wait list group data. It will also be possible to compare early versus late intervention following discharge from the community rehabilitation treatment, as the wait list participants will have a delay of 9 weeks between community discharge and beginning TIMP. Data collected from wait list group participants prior to TIMP treatment will be analyzed to determine whether there has been any spontaneous change in upper limb function, which can occur as an independent covariate (Kwakkel et al., 2006). Subject data from the ARAT and 9HPT will also be individually analyzed in order to discuss group results.

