### Sample size

The sample size of 14 stroke patients was calculated not based on a power calculation but through discussion of clinical matters between the researcher and the NHS trust hosting the study. The discussion was based on defining an appropriate number of stroke patients that would represent the heterogeneity of upper limb impairment and facilitate a report on the feasibility, management and efficacy of the intervention under the stated research conditions (unknown music based treatment, in participants' homes, twice weekly). The sample size is considered feasible for the researcher to deliver with the available time scale and resources within the host NHS trust, including staff assisted access to patient records, identification of suitable patients and invitation to participate from NHS community stroke team therapists, and completion of data collection within a limited period of time. Risks, benefits and the logistics of delivering treatment in the home, given that it is labor intensive and delivered by the researcher alone, will be observed and reported, together with participant compliance. The home environment will introduce variables that cannot be controlled for, such as space available to set up equipment, management of seating equipment to optimize positioning for the intervention, distractions in sessions such as the activities of family members or other residents present in the home. The instruments will not be set up permanently, as would be the case in a research lab, where instrument height and distance from participant can be maintained and standardized. In this study TIMP will be delivered at a frequency much lower than has been the case in existing research of this nature, so effects at this dosage are not known. All of these logistical factors warrant detailed examination in a smaller feasibility study prior to moving to a study with a larger number of participants.

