## EEG analysis

EEG case analysis of the pre/post *resting state* EEG recordings will be treated with NeuroGuide Software (www.appliedneuroscience.com; Version 2.6.6) including an age, gender and condition-matched (*N* = 678 matched controls) LORETA normative EEG database (Thatcher et al., 2005). Continuous, artifact-free, raw EEG data will be subjected to a power spectral analysis (PSA) to calculate raw and z-scored spectral values, topography (Absolute power and Current Source Density), electrode correlation, burst metrics (burst number, amplitude, duration, and interval), instantaneous connectivity and coherence patterns, especially beta coherence. Due to the small sample size (*N* = 2) we do not expect significant differences between subjects' resting state displayed on central and temporal leads in beta power *z*-score topography and coherence data in the early compared to delayed intervention. However, we do expect intra-subject pre/post intervention z-score decreases in temporal and central leads. Topography will explore post-therapy spectral power in-, or decreases in central and temporal areas; coherence data of central and temporal leads will inform about post-therapy connectivity decreases or increases between motor and auditory cortex (as seen in beta coherence; Altenmüller et al., 2009). Pre/post intervention paired *t*-test will indicate the probabilities and directions of change. We expect the post-intervention measures to show a lowering of *z*-scores, i.e., normalization, and an increase of brain connectivity between central and temporal regions.

Low Resolution Tomography (LORETA), a specific mathematical solution to EEG source localization (Pascual-Marqui et al., 1994), will inform about raw and z-transformed current density means and their pre/post differences (subtraction/individual paired *t*-test) especially of the beta range. Further raw and z-transformed Region of Interest (ROI) correlations of primary and pre-motor [Brodmann Area (BA) 4,6, Pre central gyrus], auditory (BA 22, 41, 42, superior and transversal temporal gryus) and frontal (BA 44, 45, inferior frontal gyrus) cortices will inform about post-treatment related neural reorganization in audio-motor coupling, expected to be shown as increased ROI correlations.

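### A one-course wait-list trial is labelled and analysed as a crossover; a conventional on/off coding could return as little as half the effect if gains persist

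*Protocol article*

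**What the plan says.** Study design: "A cross-over design with repeated measures will be used, with participants being randomized into either a wait list or treatment group". The abstract gives the split: "randomized into either a treatment (*n* = 7) or wait list control (*n* = 7) group".

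Procedure: "Each participant will have a total of 12 individual music therapy sessions in their home, delivered twice weekly over the course of 6 weeks". After the first assessment at Week 1, the visits are "timepoint 2 at week 6; timepoint 3 at week 9; timepoint 4 at week 15; and timepoint 5 at week 18". With the Figure 1 caption, this places TIMP in Weeks 1–6 for the early arm and Weeks 9–15 for the wait list. The same section says: "The design will allow analysis of treatment and no treatment by comparing treatment group with wait list group data". It also says that wait-list data from before TIMP will be used to look for spontaneous change.

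Statistical analysis says that, for the primary outcome, "for the appropriate analysis of the crossover design with repeated measures, a linear mixed model approach will be used". The main result is whether the therapy has had an effect. The section names the software, the bootstrap and permutation tests. It does not say how treatment is coded or which visits form the contrast.

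The expected mechanism is neuroplasticity (Background). In EEG analysis, source correlations "will inform about post-treatment related neural reorganization in audio-motor coupling". No washout, carryover term or return to baseline is mentioned.

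On assessment, Study design and the Figure 1 caption place the blind assessor at Weeks 1 and 6 for the treatment arm and at Weeks 9 and 15 for the wait list. Participants says that the assessor is blinded and that a script to protect this is used at every assessment time point.

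**The concern.** A crossover lets a participant's off-treatment period serve as control, whichever side of treatment it falls on. That requires the effect to have worn off. Here the early arm has only its Week 1 baseline before TIMP; its visits at Weeks 9, 15 and 18 all follow a complete course. If TIMP works by reorganising motor circuits, those visits may still carry the gain.

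The main result is tied to the crossover design, and the contrast is not pinned to the weeks before the wait list is treated. An analyst who follows the label could therefore fit a treatment indicator that switches off after the early arm's course. Retained benefit would then count against TIMP, and the estimate would be pulled toward no effect. The sentence that compares the two groups does not prevent this, because it gives no time window and both groups have been treated by Week 15.

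**Working it through.** **What can be reproduced.** The sample size "was calculated not based on a power calculation but through discussion of clinical matters", so there is no power figure to check. The counts agree: 7 + 7 = 14 participants, and 2 × 6 = 12 sessions.

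**Inputs.** From the protocol: 7 per arm; visits at Weeks 1, 6, 9, 15 and 18; courses in Weeks 1–6 or 9–15. Assumed: a true effect of 1 at the end of the course, of which a share λ is retained from the next visit on. The protocol gives no λ, so it is varied from 0 to 1. The model has visit effects and a random participant intercept, with intraclass correlation (ICC) from 0 to 0.95.

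**Expected effects and treatment codes**

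| | Wk 1 | Wk 6 | Wk 9 | Wk 15 | Wk 18 |
|---|---|---|---|---|---|
| Early arm mean | 0 | 1 | λ | λ | λ |
| Wait-list mean | 0 | 0 | 0 | 1 | λ |
| Difference D (early − wait list) | 0 | 1 | λ | λ − 1 | 0 |
| Code A, on only at the end-of-course visit: difference x | 0 | 1 | 0 | −1 | 0 |
| Code B, on at Weeks 6, 9 (early) and 15, 18 (wait list): difference x | 0 | 1 | 1 | −1 | −1 |
| Code C, treated from start of TIMP onwards: difference x | 0 | 1 | 1 | 0 | 0 |

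With equal arms, the visit effects leave only the between-arm differences. Codes A and B sum to zero over visits, so the random intercept drops out and the expected coefficient is ΣxD / Σx² at any ICC.

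- **Code A:** [1 + (1 − λ)] / 2 = (2 − λ) / 2. This gives 0.50 at λ = 1, 0.625 at λ = 0.75, 0.75 at λ = 0.5 and 1.00 at λ = 0.
- **Code B:** [1 + λ − (λ − 1) − 0] / 4 = 0.50 at every λ. At λ = 1 the whole shortfall is carryover. At λ = 0 it is fading within visits coded as treated. In between it is a mixture.
- **Code C:** at λ = 1, D equals x and the result is 1.00. At λ = 0.5 it is 0.75 (ICC 0) to 0.914 (ICC 0.95).
- **Change within each course window (Weeks 1–6 and 9–15):** [(1 − 0) + (1 − (λ − λ))] / 2 = 1.00. If instead the early arm loses half its gain between Weeks 9 and 15, it is (1 + 1.5) / 2 = 1.25.
- **Between-arm difference at Week 6:** 1 − 0 = 1.00 for any λ.
- **Between-arm difference at Week 9:** λ − 0 = λ. This is still a randomised comparison, of what remains three weeks after the course.

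**Precision at λ = 1, in units of the total SD.** At ICC 0.8 the standard error is 0.338 for the between-arm Week 1–6 change and 0.215 for code C. At ICC 0.9 the figures are 0.239 and 0.153. The ratio is about 1.6 (0.338 / 0.215 and 0.239 / 0.153). Code A has standard error 0.169 at ICC 0.8 but estimates half the effect, so its signal-to-error ratio is the same: 0.5 / 0.169 ≈ 1 / 0.338 ≈ 2.96.

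**The case against.** The strongest reply is that the harmful coding is nowhere written. Statistical analysis names a flexible mixed model and stops there; detailed model terms may sit in a document not shown. Procedure names the wait list as comparator and uses its pre-TIMP data to judge spontaneous change, which fits a sound delayed-start analysis. The blinded assessments bracket each course, so a change-based reading is at least as natural, and under full persistence neither that analysis nor code C is attenuated.

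Much of this stands. A reader might infer that the protocol uses the early arm's later weeks as control, or that it offers no carryover-free comparison. The text supports neither. A reader might also infer that the main estimate will be halved, but that needs both on/off coding of scores and full persistence. Persistence is not given: the Discussion says the effect at this dose is unknown, and the EEG passage concerns pre/post recordings in two participants. Nor is retention a stated aim of the later visits.

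It is also tempting to say that a halved estimate would mis-size the larger trial. At an assumed standardised effect of 1.0, two-sided 5% and 80% power, halving would raise the need from 16 to 63 per arm. But the abstract promises data on recruitment, adherence and variability of outcomes, and no passage says that this effect estimate will be used.

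What survives is that the text goes beyond silence. It commits the main result to a design class whose usual requirement, that the effect wears off, sits badly with the protocol's own mechanism. The alternative analyses also rely on the pattern of fading, as 1.25 for within-period change and 0.75 to 0.914 for code C show. The arm difference before the wait list is treated does not.

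One objection bears on the remedy. On the Figure 1 caption, Week 6 scores are blind-assessed in the treatment arm but not listed as such in the wait list, and at Week 9 the reverse holds. Freedom from carryover is therefore not freedom from assessment bias.

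**Conclusion.** The concern holds in a conditional form. The design is a randomised wait-list (delayed-start) trial under a crossover label, its main result is tied to that label, and neither the contrast window nor any carryover handling is given. Under conventional on/off coding of scores, the expected estimate is 0.50 of the true effect with full persistence, and 0.75 (code A) or 0.50 (code B) with half persistence; part of the last figure reflects fading rather than carryover.

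These sizes rest on an assumed λ, visit effects, a random intercept and complete data. They do not show that the trial will be analysed this way. The Week 6 difference between arms equals the full end-of-course effect for every λ, provided that both arms are assessed alike.

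**What to change.** - Describe the design as a randomised wait-list (delayed-start) trial in the abstract, Study design and Statistical analysis.
- Make the main estimate the between-arm ARAT difference at Week 6, supported by Week 9, both before the wait list starts TIMP. Take it from the same mixed model, with arm-by-visit means, visit effects and baseline adjustment.
- Do not code the early arm's Weeks 9–18 as untreated; report them as post-treatment follow-up.
- Report the wait-list change from Week 9 to Week 15 as secondary and non-randomised.
- Reconcile the Figure 1 caption and Study design with Participants on who is assessed blind and when, so that the scores in the main contrast are obtained alike in both arms. Otherwise state the difference as a limitation.

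The design and model changes need only wording and coding, with no new visits. If the blind assessor is not already planned at Week 6 for the wait list and Week 9 for the early arm, adding those assessments would cost assessor time. The statistical price is that the wait-list within-person change leaves the main test. In the illustrative calculation, the standard error is about 1.6 times that of a five-visit treated-from-start model under full persistence. That model can be kept as a secondary analysis, with its dependence on persistence stated.

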## EEG analysis

EEG case analysis of the pre/post *resting state* EEG recordings will be treated with NeuroGuide Software (www.appliedneuroscience.com; Version 2.6.6) including an age, gender and condition-matched (*N* = 678 matched controls) LORETA normative EEG database (Thatcher et al., 2005). Continuous, artifact-free, raw EEG data will be subjected to a power spectral analysis (PSA) to calculate raw and z-scored spectral values, topography (Absolute power and Current Source Density), electrode correlation, burst metrics (burst number, amplitude, duration, and interval), instantaneous connectivity and coherence patterns, especially beta coherence. Due to the small sample size (*N* = 2) we do not expect significant differences between subjects' resting state displayed on central and temporal leads in beta power *z*-score topography and coherence data in the early compared to delayed intervention. However, we do expect intra-subject pre/post intervention z-score decreases in temporal and central leads. Topography will explore post-therapy spectral power in-, or decreases in central and temporal areas; coherence data of central and temporal leads will inform about post-therapy connectivity decreases or increases between motor and auditory cortex (as seen in beta coherence; Altenmüller et al., 2009). Pre/post intervention paired *t*-test will indicate the probabilities and directions of change. We expect the post-intervention measures to show a lowering of *z*-scores, i.e., normalization, and an increase of brain connectivity between central and temporal regions.

Low Resolution Tomography (LORETA), a specific mathematical solution to EEG source localization (Pascual-Marqui et al., 1994), will inform about raw and z-transformed current density means and their pre/post differences (subtraction/individual paired *t*-test) especially of the beta range. Further raw and z-transformed Region of Interest (ROI) correlations of primary and pre-motor [Brodmann Area (BA) 4,6, Pre central gyrus], auditory (BA 22, 41, 42, superior and transversal temporal gryus) and frontal (BA 44, 45, inferior frontal gyrus) cortices will inform about post-treatment related neural reorganization in audio-motor coupling, expected to be shown as increased ROI correlations.

A previous study observed post therapy changes in motor and auditory activity during the music listening (Altenmüller et al., 2009; Rojo et al., 2011). In this study we will compare the pre/post *music listening data* of TIMP patterns employed in the intervention. In Rojo's study, when the participant listened to the music played in sessions after the MST treatment period, they displayed an increase of motor and auditory responses when compared to listening before they had received any MST. We hope to demonstrate the same tendencies by utilizing topographic EEG mapping and LORETA. Differences in power means and probabilities of change will inform us about differences in responses to the particular TIMP patterns.

We will analyse the particular raw pre/post means and differences of listening sequences (see Table 1) on topography shifts (Absolute power and CSD), electrode correlation (PCC), burst metrics, instantaneous connectivity, phase and coherence patterns in particular on the beta range (Altenmüller et al., 2009). Altenmüller further investigated alpha ERD/S measured after hitting a trigger pad and was able to show differences in the response latencies. Increases in frontal midline theta (FMT) triggered by emotional responses during music listening have been reported in several music therapy studies (Sammler et al., 2007; Lee et al., 2012; Fachner et al., 2013; O'Kelly et al., 2013). We expect to see more increases in FMT post TIMP treatment (6 weeks). We will apply LORETA ROI correlation of beta, alpha and theta frequency power means for each TIMP pattern (see Table 1) to indicate task related pre-post changes in auditory, frontal and motor regions (see rest EEG analysis).

**Table 1 T1:** **TIMP chart**.

	**Target movement (bold) and associated muscle groups**	**Instrument/s and equipment**	**Positioning**	**Participant instructions**	**Playing pattern**	**Facilitating music**	**Variations**
1	Single beat with affected side: **Elbow and shoulder flexion and extension, shoulder abduction and adduction**. Some wrist extension or deviation, finger extension, wrist between pronation and supination, core muscles	**14” Cymbal on boom stand**, adaptive beater and wooden drum stick, or finger picks slotted over thumb and/or finger/s	Cymbal positioned at a distance and height that the participant can reach to play Gradually raise height/increase distance and angle to facilitate increased movement range	Relax shoulders, feet flat as possible on floor/foot rests. Extend arm and fingers to cymbal. Relax and rest hand on lap or by side after playing Prompt can be sung to music: “reach and reach and play, relax”	Affected side always play on beat 3 of each bar	C, C, Am, Am, F, G, C, C 8 bar chord sequence in 4/4 Arpeggiating and building the intensity of each chord toward beat 3 Each cycle of the sequence requires 8 beats of the cymbal	**A**: using hand/fingers/finger picks **B**: adaptive beater or drum stick **C**: alternating affected and unaffected side (bell of cymbal on one beat)
2	2 successive beats with affected side: **Elbow flexion and extension**, slight shoulder extension and adduction, wrist between pronation and supination, grip, core muscles	**Cymbal on boom and bongos on stand,** adaptive beater and 2 X wooden drum sticks, finger picks	Bongos on affected side, at achievable height and angled so that larger one is further from participant, cymbal for unaffected side. Gradually reposition for increased range of movement	Try to focus on elbow bending and stretching Relax shoulders, feet flat as possible on floor, reach arm (and fingers). Relax arm and rest hand on lap after playing Sung prompt: Left (affected) and left and right, relax	In 6/8, play on the underlying pulse: affected hand plays bongo 1, then 2	Rhythmic, energetic, jazz idiom: G7, G#Dim, Am7, D7, played in 6/8 over 4 bars. Arpeggiated and/or strummed with strongly accented beats Each cycle of chords requires 6 beats on the percussion (4 on affected side)	**A:** using hand/fingers/finger picks **B:** adaptive beater (affected) drum stick (unaffected) **C:** drum stick both hands
3	3 successive beats with affected side: **Shoulder and elbow flexion, and extension**, **shoulder abduction**, slight shoulder adduction, wrist between pronation and supination, grip, core muscles	**Cymbal on boom and bongos on stand,** adaptive beater and wooden drum sticks, finger picks	Bongos on affected side (as above), adjusting the height and positioning of instruments to facilitate greater shoulder and elbow extension or shoulder abduction	Try to focus on elbow bending and stretching Sung prompt: Left (affected) and left and left and right	In 6/8, play on underlying pulse: affected side plays bongo 1, then 2, then cymbal, then unaffected side plays cymbal bell (hitting the centre of the cymbal)	Any 1, 6, 2, 5 chord sequence played over 4 bars. Strongly pulsed arpeggios or strummed rhythm in 6/8 Each cycle of chords requires 8 beats on the percussion (6 on affected side)	**A:** using hand/fingers/finger picks **B:** adaptive beater (affected side) and drum stick (unaffected) **C:** two drum sticks
4	4 successive beats with affected side: **Shoulder and elbow flexion and extension**, **shoulder abduction**, slight shoulder adduction, wrist between pronation and supination, grip, core muscles	**Cymbal on boom and bongos on stand,** adaptive beater and wooden drum sticks, finger picks	Bongos on affected side (as above), adjusting the height and positioning of instruments to facilitate greater shoulder and elbow extension or shoulder abduction	Try to focus on elbow bending and stretching Sung prompts as TIMP 2 and 3	In 6/8, on underlying pulse: affected side plays bongo 1, then 2, then cymbal, then cymbal bell, unaffected side then plays the pattern in reverse order	Any 1, 6, 2, 5 arpeggiated or strummed chord sequence played over two bars, strongly pulsed rhythm in 6/8 Each cycle of chords requires 8 beats from the affected side	**A:** using hand/fingers/finger picks **B:** two drum sticks, affected side plays the pattern, then unaffected side plays pattern in reverse while affected side rests
5	Bilateral playing, crossing midline: **Shoulder adduction, extension and flexion**, **elbow flexion and extension**, grip, wrist between pronation and supination, core muscles	**Cymbal on boom and bongos on stand,** adaptive beater and wooden drum sticks, finger picks	Bongos on affected side, cymbal on unaffected side Distance of instruments from participant and width apart of instruments varies, to facilitate increases in shoulder adduction and extension	Feet flat as possible on floor, try to relax shoulders and achieve smooth twisting action at shoulders and torso to play left and right	Both hands crossing midline alternating affected and unaffected side on beat 3 of each bar, progressing to beats 1 (L) and 3 (R)	Open “A” bass note played over arpeggiated or strummed chords: A, Bm, C#m, Bm, Played with clear pulse, 4/4 time over two bars	**A:** using hand/fingers/finger picks **B:** adaptive beater (affected) and drum stick (unaffected) **C:** two drum sticks
6	Fine motor: thumb only or thumb and index, middle or ring finger gripping a plectrum **Thumb extension and flexion**	**Tablet and Garageband** music software using “Smartguitar,” tablet touch screen plectrum, speaker connected	On lap on affected side, on stand at appropriate height, or on table top	Fingers rest on the side of the tablet, the thumb extends side to side across the screen strings Participants aim to strum across as many strings as possible with each thumb stroke, in time to the beat	Chord strummed using thumb only on beat 1 and 3 until final bar (C), which is beat 1 only	C, F, G, C sequence in 4/4. Each played with bass “lead in” as follows: g, a, b, **C** (*chord*), c, d, e, **F** (*chord*), f, e, d, **G** (*chord*), g, a, b, **C** (*chord***)**	**A:** up and down stroke with thumb, twice on each chord, including final chord strummed 4 times **B:** holding the tablet plectrum using the thumb and index, middle or ring finger and strumming across the strings
7	Fine motor control of fingers or arm: single or two finger combinations using various fingers, or pinch grip **Shoulder stabilization, finger extension (any/all finger/s or part of finger), wrist deviation,** elbow extension, wrist extension	**Tablet and Garageband** with “Smartpiano,” sustain switch on, chords set to G (Left side of screen) and G, D5, G in centre of screen, speaker connected. Alternatively, Smartguitar using the plectrum	In line with affected side. At a height approximate to a standard keyboard height, or that does not demand participant to extend arm excessively to reach the keys In some instances placing the tablet on the participant's lap or a table (affected side) may offer the most accessibility and focus on finger extension	Relax shoulders, reach with your finger/s, feet flat as possible on floor Participants may initially trigger the sounds using knuckle or other part of finger The therapist should encourage and support use of finger tips where possible	tablet: playing a single “G” chord by sliding fingertip/s, knuckle, etc., vertically upwards over the chord and/or slightly away from body Alternating affected and unaffected side, 1^st^ beat of each bar	Frere Jacques in G major with strong pulse	**A:** unaffected fingers play the G, D5, G, chords on “ding, dang, dong” lyric section of song **B:** affected side plays G, D5, G section **C:** affected hand uses index, then middle finger to play “G” unaffected hand plays G, D5, G section **D:** using the tablet plectrum and Smartguitar
8	Fine motor control: single to 4 finger combinations **Finger movements or finger extensions**, shoulder stabilizing, elbow flexion and extension, shoulder extension, abduction and adduction. Core muscles	**2 X tablets**: both mounted on a single microphone stand Garageband music software using “Smartpiano.” Tablets connected to speaker using two mini jack leads and a splitter input	Tablets one above the other or next to each other, mounted on two tablet clamps which are both on the same microphone stand	Initially, therapist instructs participants whilst playing the chords by singing the chord names or “play” each time the participant is required to play the next chord.	Any finger or finger combination playing each chord individually in time to the music. Finger can extend to play ascending chord or flex to play descending chord (down the screen)	8 chord sequence played to accompany the alternating chords on tablet 1 and tablet 2 as follows: C, G, Am, Em, F, G, C, C. with each chord arpeggiated. Clear accents on bass note of each chord to emphasize pulse	**A:** single finger extension alternating left and right hands **B:** single finger extensions, affected hand only **C:** 2 fingers alternating left and right hands (index L, index R, middle L, middle R, etc) **D:** alternating left and right hands using 3 fingers (as above) **E:** alternating left and right hands using 4 fingers (as above)
9	Fine motor control: single to 4 finger combinations or thumb and finger pinch grip using tablet plectrum **Finger movements or finger extensions,** Thumb, Index, middle and ring finger extension and flexion, shoulder stabilization, elbow flexion, core muscles	**Tablet:** Garageband music software, “Smartbass” or “Smartguitar” and speaker, mounted on stand or resting on lap or table top, tablet plectrum	Tablet positioned in portrait rather than landscape in order to facilitate “keyboard” style finger patterns on the strings. Position on stand, lap or table top	Relax shoulders, feet flat as possible on floor Initially, sing each chord name	Playing on the first beat, then 1 and 3, then 1, 2, 3.	Chord sequence: C. G. Am, Em, F, G, C:||4/4, (one chord per bar)	**A:** index **B:** index and middle **C:** index, middle ring **D:** index, middle, ring, little finger **E:** thumb, index and other fingers **F:** using tablet plectrum held using thumb and index, middle or ring finger and used to play individual notes on each string or chords
10	Fine motor control: single to 2 finger combinations **Finger movements or finger extensions,** finger, wrist, elbow or shoulder extensions, some shoulder abduction or adduction depending on positioning	**Tablet:** mounted on the boom stand, speaker connected. ThumbJam Cello, E3 to E4, major scale setting	Mounted on stand in portrait position, so that as the fingers move up the screen, the scale ascends	Keep finger in contact with screen for the full duration of the music, moving it up/changing finger in time with the music Sing “play” to participants each time they are required to move to the next note	Playing up the screen: E, F#, G#, A, B, C#, D#, E	Ascending scale: E, B, E, A, E, A, B, E. Descending scale: E, B, A, E, A, E, B, E. Arpeggiating the chords and with a “turn around” phrase at the end to indicate “back to the start note (E)” For example the notes: b, c#, d# on the “B” string	**A:** hold position sustaining the top “E” note of the scale at the top of the screen, then following the music to descend back down the screen to bottom note “E”
11	^1^(Baker et al., 2006) **Grip, wrist ulnar and radial deviation**, elbow flexion	**Cabasa**: small, medium and large sizes **Bongos or cymbal** on stand	Cabasa held in unaffected hand, affected hand aims to grip the beads over the top/round the side with any finger/thumb combination and twist to produce sound	Relax shoulders, “twist, release, reach, play” (spoken or sung to participants in-time with music)	Playing on 1^st^ (cabasa twist) and 3^rd^ (bongo/cymbal) beat of each bar	Strongly pulsed, rhythmic and staccato music, for example Spanish idiom using E, F/E bass, 4/4 time	**A:** grip and twist cabasa with affected hand on beat 1, then release it and hit the cymbal on beat 3 using the affected hand (no stick or beater)
12	**Wrist and forearm pronation and supination,** shoulder adduction, elbow extension, core muscles	**Cymbal on boom and bongos on stand,** two drum sticks or beaters taped together so there is a tip at either end or single stick/beater rotated so that tip plays cymbal then bongo	Cymbal and bongos slightly less than a beater's distance apart focusing efforts on wrist and forearm rotation Alternatively, play bongos, rotating wrist/forearm to play bongo 1 then bongo 2	Sung prompt: turn and turn and play	Affected hand only plays bongo with one end of the stick, then cymbal or bongo 2 with the other end on beat 3 only (slow rotation) or 1 and 3	Octaves or chords: F slide to C, slide to Gm, slide to Dm 4/4 time over 2 bars, with strong accent on beats 1 and 3 and crescendo between each chord	**A:** holding just the adaptive beater and making full forearm pronation and supination movement to play cymbal then bongo or bongo 1, bongo 2 **B:** using a cabasa instead of stick/beater

*Patterns gradually increase in complexity; 1–5, gross motor; 6–10, fine motor; 11 and 12, grip and release, pronation and supination*.

A Go/No Go *task* will be performed to track improvements in reaction time (measuring participant's response to visual stimuli with a button press) and changes in contingent negative variation (CNV) between signals as a marker of attention processes. We expect the reaction time to have shortened more in the early intervention group.

